### Statistics

#### Sample size calculation

The primary endpoint of this study protocol is to assess equivalence of the protrusive position obtained with the three titration protocols. We need 65 patients to have 80% power to show equivalence of two procedures with an equivalence margin of 1.6 and a standard deviation of 3.7. These numbers are based on the results of Civelek et al. [12]. The significance level of 0.05 will be Bonferroni corrected to 0.0167, to account for comparing three titration protocols.

For every patient dropping out of the study before the first visit, an extra patient will be recruited. Based on previous studies, the dropout rate is anticipated to be around 20%, so we expect to include 78 patients in total.

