Therapy with continuous positive airway pressure (CPAP) is the standard nonsurgical treatment option for patients with moderate to severe OSA [10]. CPAP therapy prevents upper airway collapse by providing a pneumatic splint using a constant positive pressure at the level of the collapsible segment of the upper airway throughout the respiratory cycle [11]. The amount of pressure required to avoid upper airway collapse cannot be predetermined based on OSA severity and needs to be assessed individually. To achieve the optimal pressure alleviating the disease, the current standard practice involves an overnight attended CPAP titration polysomnography (PSG) in which the applied pressure is manually increased by a sleep technician each time respiratory events occur [12]. Rather than the use of an overnight attended PSG to find the optimal CPAP pressure, an unattended auto-titrating CPAP device can be used for several nights [13, 14]. Auto-titrating CPAP devices continuously monitor the patient’s snoring, airflow and flow limitation, and provide variable CPAP pressures in accordance with respiratory events using an algorithmic approach. As such, these devices can be used either to treat a patient with different pressures delivered during different sleeping conditions, in response to differing degrees of upper airway obstruction in these states, or to identify the most appropriate fixed CPAP pressure level. More recently, Civelek et al. [12] proposed to titrate the CPAP pressure under direct visualization of upper airway collapse during drug-induced sleep endoscopy (DISE). DISE enables a dynamic, three-dimensional, real-time evaluation of the anatomical sites of upper airway collapse during drug-induced sleep which ideally mimics natural sleep, although without REM sleep being present [15]. This DISE-assisted titration showed comparable results regarding the optimal CPAP pressure that alleviates OSA as compared to the conventional titration PSG. Overall, once the optimal pressure is determined, CPAP therapy is highly efficacious in terms of alleviation of OSA severity. However, the high clinical efficacy can be compromised by low patient acceptance or suboptimal adherence, thereby limiting the overall clinical effectiveness of this therapy [16].

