#### Exclusion criteria

◦ Edentulous patients◦ Insufficient teeth to support MAD◦ Active periodontal problems including tooth mobility◦ Active temporomandibular joint dysfunction◦ Limited maximum protrusive capacity (< 6 mm)◦ Limited vertical opening (< 25 mm)◦ Enlarged palatine tonsils (Friedman grade IV tonsils)◦ Degenerative neuromuscular disorders◦ Pregnancy

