## Discussion

Mandibular advancement devices are a valuable nonsurgical treatment option for patients diagnosed with OSA. The literature has shown that the amount of mandibular protrusion is a key factor in optimizing MAD efficacy and that the final titration of the protrusion should be carried out individually, trying to find the most effective protrusion, whilst at the same time respecting the patient’s physical limits [20, 39]. However, there is still no consensus on the optimal titration method.

The conventional approach relies on improvement of subjective symptoms, such as snoring and/or daytime sleepiness, for guidance of the titration toward the ideal mandibular protrusion in the individual OSA patient [24–27].

A more objective approach includes the use of an RCMP during a full-night PSG: in a process analogous to a CPAP titration night, the mandible is progressively advanced during sleep each time respiratory events occur throughout the night [21]. However, this is a time-consuming, labor-intensive and expensive procedure, because of the need for an overnight and attended hospital stay [12].

Civelek et al. [12] studied the effect of modulated CPAP pressure on upper airway collapsibility under direct visualization applying DISE. This DISE-assisted titration showed comparable results regarding the optimal CPAP pressure that alleviates OSA as compared to the conventional titration PSG. However, the titration procedure during DISE was found to be less labor-intensive and time-consuming as compared to a titration PSG [12].

The present randomized crossover trial will assess the mandibular protrusion values of MAD treatment under DISE-assisted titration using RCMP and compare these to the values obtained using a titration PSG, as well as with those obtained using the conventional subjective titration method. Furthermore, if different mandibular protrusion values are obtained according to the studied titration methods, it will be possible to compare the efficacy using level 1 sleep studies recorded at the end of each procedure.

Ideally, the same titration protocol for the DISE-assisted titration and the titration PSG is considered. However, due to the technical limitations of both procedures, some minor adaptations were made to the DISE-assisted titration protocol compared to the titration PSG as described earlier in the Methods section of this manuscript.

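### The primary equivalence margin (1.6) and SD (3.7) for mandibular protrusion carry no unit and are credited only to a CPAP-pressure study, so the 80% power is not established for protrusion

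*Protocol article*

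**What the plan says.** Under Sample size calculation, the protocol article gives the primary aim as to "assess equivalence of the protrusive position obtained with the three titration protocols". The section asks for 65 patients at a power of 80%, and it describes the target of that calculation in these words: "to show equivalence of two procedures with an equivalence margin of 1.6 and a standard deviation of 3.7". Significance is set at 0.0167 after a Bonferroni correction for three procedures. On where the margin and SD come from, the section has one sentence, which opens "These numbers are based on the results of" and cites reference 12.

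The same article describes reference 12 twice. The Discussion says that it "studied the effect of modulated CPAP pressure on upper airway collapsibility under direct visualization applying DISE". The Background reports that DISE-assisted titration in that study gave "comparable results regarding the optimal CPAP pressure that alleviates OSA" when set against a conventional titration PSG.

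The trial's own endpoint is the protrusive position of the mandible. The Methods handle it in millimetres: 0.5 mm steps in the PSG titration, and 2, 1 and 0.5 mm steps in the DISE titration.

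**The concern.** The margin and the SD belong to an outcome measured as a displacement of the jaw. Their only stated source, as the article itself describes it, compared an air pressure. A study on another physical scale cannot by itself say which difference in protrusion is unimportant, or how much protrusion varies within a patient between two titration methods. The article offers no step from one scale to the other, and without a unit the reader cannot tell on which scale 1.6 and 3.7 are meant to be read.

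Two things depend on these figures. The first is the primary conclusion: this is the only place in the article where a margin for the primary endpoint appears, so a claim that two procedures give equivalent positions would be judged against it. The second is the stated 80% power, which rests on the ratio of margin to SD. The margin matters more. A smaller SD than planned would raise the power, but it would not supply a reason for the margin.

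**Working it through.** **Inputs from the article (Sample size calculation).** Margin Δ = 1.6; SD σ = 3.7; alpha = 0.05/3 = 0.0167; power 80%; n = 65. The article does not say whether 3.7 is the SD of a single measurement or of a within-patient difference.

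**Step 1: reproduce 65.** Take two one-sided paired tests, each at alpha 0.0167, with a true difference of 0 and σ as the SD of the within-patient difference.

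Normal approximation: n = [σ(z₁₋α + z₁₋β/2)/Δ]², with z(0.9833) = 2.127 and z(0.90) = 1.282:

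n = [3.7 × 3.409 / 1.6]² = 7.883² = 62.1, so 63.

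The exact calculation replaces z by the t quantile and averages over the distribution of the estimated SD. It gives 79.6% at n = 64 and 80.5% at n = 65. So 65 is the smallest n that reaches 80%, and the stated figure reproduces exactly.

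Other readings do not give 65 (normal approximation, rounded up):

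| Reading | n |
|---|---|
| 0.05 per side | 46 |
| 0.025 per side | 57 |
| 0.00835 per side | 73 |
| 3.7 as SD of each of two independent measurements (variance doubled) | 2 × 62.1 = 124.3, so 125 |

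The calculation is therefore correct for its inputs, and 3.7 was in effect used as the SD of the within-patient difference.

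**Step 2: set the source beside the use.**

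| | Quantity | Scale |
|---|---|---|
| Source of 1.6 and 3.7 (reference 12, as described in Background and Discussion) | Optimal CPAP pressure, DISE against titration PSG | Pressure |
| Use of 1.6 and 3.7 (Sample size calculation) | Protrusive position, three procedures compared in pairs | Millimetres in the Methods; no unit in the calculation |

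No sentence links the two rows.

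**Step 3: what the power at n = 65 would be on the protrusion scale.** The article gives no SD and no margin derived from protrusion data, so every row below is an assumption, except the one that reads the plan's own figures as millimetres. Same exact paired method, alpha 0.0167 per side, true difference 0. The last column uses the normal approximation of step 1.

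| Margin (mm) | SD of difference (mm) | Power at n = 65 | n for 80% power |
|---|---|---|---|
| 1.6 | 3.0 | 96% | 41 |
| 1.6 | 3.7 (plan's figures) | 80.5% | 63 |
| 1.6 | 4.5 | 51% | 92 |
| 1.0 | 2.0 | 93% | 47 |
| 1.0 | 2.5 | 70% | 73 |
| 1.0 | 3.0 | 39% | 105 |

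Example, margin 1.0 and SD 3.0: n = [3.0 × 3.409 / 1.0]² = 104.6, so 105. Over these assumptions the power lies both well above and well below 80%.

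**The case against.** The strongest reply has four parts.

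*The source has not been seen.* The article says only that the figures are based on that study's results. They may have been derived or rescaled. This stands: the documents do not show that pressure values were carried over unchanged, and a reader should not infer it. What they do show is that the only named source measured pressure and that no bridge to protrusion is stated.

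*Nothing shows that the figures are wrong for protrusion.* This also stands, and it rules out two tempting inferences.

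- A reader might note that an SD of 3.7 mm puts 95% of differences within 1.96 × 3.7 = 7.3 mm either way, set this against the 6 mm in the exclusion criterion "Limited maximum protrusive capacity", and call the SD implausible; or call the margin too wide as a share of that 6 mm. But 6 mm is the floor for eligibility. The article gives no mean or upper limit for the range of the patients enrolled.
- A reader might argue that, were the SD smaller, 65 patients could support a tighter margin, so 1.6 is lax. But an equivalence margin is set by what difference is unimportant, not by the tightest limit that the sample could support. The 0.5 mm step is likewise the resolution of the titration and not a threshold of clinical importance.

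*The low-power rows are not evidence.* They are assumptions, and nothing in the article points to an SD above 3.7. They show sensitivity only.

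*A full protocol or analysis plan may justify the margin.* That would excuse a missing rationale. It does not excuse a rationale that the article does state and that, by its own description, concerns another outcome.

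**Conclusion.** The point holds, and it concerns the stated basis of the margin and SD. It does not concern the arithmetic: 65 follows from the inputs, with 80.5% power. The only equivalence margin given for the primary endpoint, and the SD behind the power, are unitless and attributed to a study of CPAP pressure, with no conversion and no reason specific to protrusion. The stated 80% power is therefore not established for protrusion.

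The size of the error cannot be fixed from the documents, nor can its direction. With 65 patients and a margin of 1.6 mm, moving the assumed SD from 3.0 to 4.5 mm takes the power from 96% to 51%. With an assumed margin of 1.0 mm, moving the SD from 2.0 to 3.0 mm takes it from 93% to 39%. These figures rest on a paired analysis, a true difference of zero and alpha 0.0167 per one-sided test.

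It would go too far to conclude that 1.6 mm is too wide, that 3.7 mm is impossible or that 65 patients are too few. Any of the plan's figures may prove defensible once argued on the right scale. It needs to be put right because the margin decides the primary claim and cannot credibly be set after the results by procedure have been seen.

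**What to change.** Before any comparison by procedure:

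1. State the unit of the margin and of the SD, and say that the SD is that of the within-patient difference.
2. Set the margin in millimetres, or as a percentage of maximal protrusion, with a reason based on what difference in protrusion is unimportant.
3. Take the SD of within-patient differences from protrusion data, or from a blinded pooled estimate in this trial's patients.
4. Restate the power at n = 65 over a plausible range of SDs.
5. Stop citing the CPAP study as the basis for either number.

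The cost is a rewritten sample size section and one blinded variance check. The restated power may fall below 80%, and a tighter margin may show that 65 patients give less power than stated. The sponsor would then have to choose between reporting the lower power and recruiting more patients.

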### Study protocol

After inclusion, each patient will undergo three different titration procedures of the protrusive mandibular position, in a randomized order: subjective titration; RCMP titration during DISE; RCMP titration during PSG (see Fig. 1).

In our study, a commercially available RCMP (MATRx™; Zephyr Sleep Technologies Inc., Calgary, Canada) will be used [21]. The RCMP uses dental trays filled with high-viscosity impression material that fit retentively over the teeth to allow for progressive titration of the mandible during sleep, without arousing the patient. It consists of a controller that receives commands from the device software and, in turn, activates a stepping motor attached to dental trays in the patient’s mouth (Fig. 3). The positioner (50 g; 62 mm × 41 mm × 20 mm) has two movable rods that connect to brackets extending anteriorly from the dental trays. The upper rod is driven by an internal linear actuator and attaches to the upper bracket. The lower rod is driven by a manually adjustable screw and connects to the lower bracket [21]. Before the PSG-guided or DISE-assisted titration is planned, the dental sleep professional will fit upper and lower disposable dental impression trays that attach to the RCMP positioner. During that visit, the dentist will record the habitual bite position, maximum retrusion and maximum protrusion as voluntarily performed during wakefulness. These measurements will be used to set the individual’s mandibular range of motion for the RCMP studies.

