#### Statistical analyses

The primary endpoint and all continuous secondary endpoints will be analyzed using a linear mixed-effects model with period, sequence and procedure as fixed effects, and a patient nested within sequence as a random effect. For the response rate, a logistic mixed-effects model with the same specifications will be used. The response rate will be defined as a decrease in AHI of at least 50% compared to baseline or an AHI under treatment of < 15 events/h. Post-hoc comparisons will be made based on these models, correcting for multiple testing by means of Bonferroni–Holm stepdown correction.

Non-inferiority of PSG compared to DISE will be judged based on the confidence intervals obtained from the mixed-effects models. When the lower limit of the confidence interval falls above the predefined non-inferiority margin, non-inferiority will be concluded. The non-inferiority margin for the percent change in AHI from baseline will be set at 10%. For the change in VAS for snoring, the ESS, the CIS20R and its fatigue subscale the margin is considered, respectively, to be 1, 2, 5 and 10 points. Additionally, differences between subjective titration and both RCMP titration protocols will be investigated for all of the secondary endpoints.

If more than 20% of all information regarding one endpoint is missing, a sensitivity analysis will be conducted for this endpoint using multiple imputation. Results of the original analysis will be interpreted in the light of these sensitivity analyses.

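### The enrolment figure of 78 adds 20% to 65 instead of allowing for 20% dropout: 65 evaluable patients need 82 enrolled, and 78 covers dropout only up to 16.7%

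*Protocol article*

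**What the plan says.** All the figures are in the Sample size calculation section of the Protocol article.

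- Requirement: "We need 65 patients to have 80% power to show equivalence of two procedures".
- Margin and spread behind that number, without units: 1.6 and 3.7 respectively.
- Significance level: "The significance level of 0.05 will be Bonferroni corrected to 0.0167, to account for comparing three titration protocols".
- Replacement: "For every patient dropping out of the study before the first visit, an extra patient will be recruited".
- Dropout and total: "the dropout rate is anticipated to be around 20%, so we expect to include 78 patients in total".

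Two other places bear on the point. Under Study protocol, "each patient will undergo three different titration procedures of the protrusive mandibular position, in a randomized order", so the number that counts is patients with paired data. Under Statistical analyses, the primary endpoint is to be "analyzed using a linear mixed-effects model with period, sequence and procedure as fixed effects, and a patient nested within sequence as a random effect", and this model can use patients who complete only some of the periods.

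**The concern.** The total is presented as following from 65 and 20%, and it does not. Adding 20% to the evaluable number is not the same as allowing for the loss of 20% of those enrolled, and the first always gives the smaller total. If dropout runs at the rate the protocol itself anticipates, the trial ends with fewer complete patients than its power statement requires. The 65 has almost no slack under the calculation that reproduces it, so even a small shortfall takes completers-only power for the primary equivalence comparison below 80%. In an equivalence trial, lower power means a higher chance of an inconclusive result.

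**Working it through.** **Inputs, all from Sample size calculation:** required n = 65, target power 80%, margin Δ = 1.6, SD = 3.7, α = 0.0167, dropout d = 20%, total 78.

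**Assumptions not stated there:** a true difference of zero; 3.7 is the SD of the within-patient difference; each of the two one-sided tests (TOST) is run at 0.0167. Together these reproduce the stated 65.

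**Step 1. Reproduce the 65.** Exact paired TOST, t distribution with n − 1 degrees of freedom, standard error 3.7/√n:

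| n | Power |
|---|---|
| 62 | 77.5% |
| 63 | 78.6% |
| 64 | 79.6% |
| 65 | 80.5% |

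The smallest n reaching 80% is 65, as stated. Other readings do not give 65:

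- α = 0.05 gives 48, α = 0.025 gives 59, and α = 0.0167/2 gives 76.
- Two independent groups at α = 0.0167 (normal approximation) give 125 per arm.
- The normal approximation for the paired design, n = [3.7 × (z(1−0.0167) + z(0.90))/1.6]² = [3.7 × (2.127 + 1.282)/1.6]² ≈ 62.1, gives 63.

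**Step 2. Reproduce the 78.** 65 × (1 + 0.20) = 78.0, exactly.

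**Step 3. Enrolment that keeps 65.** n/(1 − d) = 65/0.80 = 81.25, rounded up to 82. This is 82 − 78 = 4 more than stated.

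**Step 4. What 78 delivers.**

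- Expected completers at 20% dropout: 78 × 0.80 = 62.4, about 62.
- Largest dropout that still leaves 65: 1 − 65/78 = 16.7%.
- If each patient drops out independently with probability 20%, the chance that at least 65 complete is about 28% with 78 enrolled and about 63% with 82.

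**Step 5. Power at 62 completers.**

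| Method | n = 62 | n = 65 |
|---|---|---|
| Exact paired TOST, df n − 1 (reproduces 65) | 77.5% | 80.5% |
| Same, with df 2(n − 1) as in a three-period mixed model | 78.7% | 81.6% |
| Normal approximation | 79.9% | 82.6% |

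The shortfall against 80% is 0.1 to 2.5 points, depending on the method. The 2.5 points belong to the method that yields the protocol's own 65.

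**The case against.** **Replacement.** The sentence before the total promises a replacement for each patient lost before the first visit. One could therefore read 78 as a forecast: 65 plus 13 replacements for 20% of 65. Part of this stands, because early losses need not reduce the evaluable number if replacement is open-ended. It does not make 78 right. If 20% of the replacements are lost as well, the total again tends to 65/0.80 = 81.25, or 82. If some of the 20% leave after the first visit, the section gives no replacement for them. The text does not say how the 20% divides between the two.

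**Dropping out is not the same as missing the primary outcome.** The primary outcome is the protrusive position. For the PSG and DISE methods it is obtained from the titration procedure, before the month of device use and the follow-up sleep study. A patient lost during that month still supplies the position, and a patient lost after two titrations supplies one complete pair. The mixed model uses such data. This stands: for any one comparison, 62 is the low end if 20% leave. How far above it the trial would land depends on the timing of dropout, which is not given.

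**Holm correction.** Statistical analyses plans a Bonferroni–Holm step-down for post-hoc comparisons, which is less strict than a fixed 0.0167. In a simulation of three paired TOSTs at n = 62, with all true differences zero, difference SD 3.7 and equal correlations, average power per comparison was about 77% with fixed Bonferroni and about 87% with Holm. The gain needs the other pairs to be equivalent too. If only one pair is, power returns to about 77.5%. The trial is also still sized at 0.0167.

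**The stronger reading.** A reader might infer that the trial fails to deliver its stated 80% power. The documents do not support that as a firm claim. The 80% is attached to 65 patients, not to 78 enrolled; the dropout rate is approximate; the break-even of 16.7% is only about 3 points below it; and the planned analysis does not discard partial data.

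**Conclusion.** The arithmetic error stands: neither reading of the dropout and replacement sentences makes 78 consistent with 65 evaluable patients and 20% dropout. The gap is 4 enrolments, or about 3 completers at the anticipated rate.

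The consequence is minor. Completers-only power falls from 80.5% to about 77.5%, and this is close to a lower bound for 62 completers at a zero true difference. It rests on the unstated assumptions listed with the inputs; a non-zero true difference would lower power at 62 and at 65 alike. The error does not touch the design, the choice of endpoint, the error control or the validity of any conclusion.

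**What to change.** Correct the sentence in Sample size calculation in one of these ways:

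1. Keep 78 and state that it allows for dropout of up to 16.7%.
2. Keep 78 and state that at 20% dropout about 62 patients are expected to complete, with roughly 77–78% power on a completers-only analysis, adding that the mixed model also uses partial data.
3. Give 82 as the enrolment that matches 65 evaluable patients at 20% dropout.

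In each case, say whether the 20% includes patients lost before the first visit, and whether their replacements are counted in the total.

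Options 1 and 2 cost one sentence and a slightly less favourable figure. Option 3 costs four more patients and is not essential. No change to design or analysis is needed.
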